### 3.3 Preclinical Evidence

Based on exhaustive OMS literature review (71), even if FTC is currently considered equivalent to 3TC, some pharmacological differences could be important in the clinical context of dual therapy. FTC has a longer half-life and a greater potency against HIV-1 compared to 3TC. FTC has superior inhibition of viral replication when combined with tenofovir (TDF) compared to 3TC+TDF combination and has a higher binding affinity for reverse transcriptase and lower affinity for mitochondrial DNA

polymerase compared to 3TC. Moreover, the development of the M184V/I mutation, which is the most common NRTI mutation, is associated to a greater extent with the use of a 3TC-rather than a FTC-containing regimen.

### 3.4 Clinical Evidence to Date

#### ***Dolutegravir efficacy data in maintenance monotherapy***

DTG monotherapy as maintenance treatment in an ART experienced population was proved to be feasible, with a high rate of effectiveness over 24 weeks in three observational studies (49, 72, 73). *Katlama et al* enrolled 28 patients virologically controlled for 6.6 years with a median nadir CD4 count of 215 cells/mm^3. The proportion of patients with viral load <50 copies/ml at week 24 was 89% (25/28 patients). Three virological failures were reported: all occurred in patients previously exposed to first generation integrase inhibitors, and patients developed signature mutations for integrase inhibitors at week 24. Patients were however switched back to conventional triple ART regimen with virological success. The study by *Rojas et al* included 33 patients, virologically controlled for 8 years and with a mean nadir CD4 count of 229 cells/mm^3 (SD ±125); 97% of patients remained with an undetectable viral load at 24 weeks. One patient, previously failing on raltegravir, demonstrated virological failure with HIV-DNA genotypic resistance test showing a signature mutation for integrase inhibitor at week 24. *Oldenbuettel et al* enrolled 31 patients virologically suppressed for 24 weeks. One patient discontinued for adverse event (ongoing cough) and one presented with virological failure at week 24. This latest patient continued on DTG monotherapy for five more weeks; the genotypic resistance test at that time showed major INSTI mutations (73).

However, an academic-driven randomized controlled trial of DTG mono-maintenance therapy (the DOMONO trial - NCT02401828) in which 104 HIV virologically suppressed patients were enrolled to an immediate or delayed (at week 24) switch to DTG monotherapy and followed throughout 48 weeks from the date of switch, was prematurely stopped because of virological failure in 10% of patients (74, 75). While DTG monotherapy was non-inferior to cART at week 24, most of virological failures occurred after week 24 and led to INSTI-associated resistance mutations in three patients.

In addition, the Data Safety Monitoring Board of the DOLAM study, an open-label randomized controlled trial (EudrCT number 2015-000274-35) which enrolled HIV-1-infected adults on stable triple antiretroviral therapy to receive cART, DTG + 3TC or DTG monotherapy, decided to interrupt the DTG monotherapy arm because of the occurrence of two virological failures in this arm (76).

Finally, the REDOMO study showed that the percentage of virological failures in three large clinical cohorts of individually switching to a DTG-mono-therapy maintenance strategy was 9%. The selection of genotypic resistance mutations in individuals failing to DTG-mono-therapy was rapid and high. The mutations selected on virological failures to DTG-mono-therapy involves different pathways of resistance to INSTI (92Q, 118R, 148X and 155H) (77).

#### ***Dolutegravir efficacy data in dual therapy (either in ART-naïve or experienced patients)***

The PADDLE study, a single-arm pilot trial for patients with HIV-RNA <100,000/ml copies at screening, demonstrated an overall efficacy of DTG-3TC of 90% as *first-line treatment*. One patient with virologic failure had an entry HIV RNA >100,000 copies and was suppressed initially, but developed low-level viremia from week 36-48; no resistance was detected (78). Bitherapy of DTG and rilpivirine was tested among 38 experienced patients who had benefited from several ART regimens. Participants presented with significant major resistant mutations to NRTIs, NNRTIs and PIs but none of them had resistance to INSTI or rilpivirine (79). All patients were virologically suppressed at week 48, showing that heavily pre-treated patients can safely be switched to simplified ART. Moreover, in vitro studies have shown that the presence of NRTIs resistance mutations M184I/V and K65R prevent the emergence of HIV-1 resistance against DTG, but not RAL or EVG (80).

The LAMIDOL study, which enrolled 104 HIV experienced patients without previous virological failure to switch to a dual maintenance therapy of DTG + 3TC (lamivudine) showed that 97% (101/104) of participants remained virologically suppressed at week 40(81). 7.7% (8/104) of participants experienced serious adverse events; only 1 patient discontinued study drugs due to suicide ideation.

A summary of the studies on DTG monotherapy and dual therapy that have been presented or published so far is given in the Supplementary Files 1 and 2.

In the SIMPL'HIV trial, we chose to evaluate the efficacy and safety of DTG + FTC dual maintenance

therapy in HIV virologically suppressed experienced patients. The choice of the combination of DTG with FTC is based on (1) the superiority of emtricitabine 200 mg once daily when compared to 3TC (lamivudine) (70), (2) the fact that no study – to our knowledge - is currently evaluating this combination, and (3) the soon generically available dual maintenance therapy combining DTG and FTC.

### 3.5 Dose Rationale

This trial will be using the dose of DTG 50mg in combination with FTC 200 mg oral per day, which corresponds to the doses recommended by the manufacturers.

### 3.6 Explanation for choice of comparator

HIV guidelines provide clear recommendations of what a first-line and maintenance regimen should be according to the latest publications (82, 83). Based on recommendations of the European AIDS Clinical Society (EACS) guidelines dated of October 2015 (84), recently updated in October 2017(63) we will accept as standard of care any of the following ART regimens that achieved viral suppression for at least 24 weeks, i.e.:

- 2 NRTIs + either 1 NNRTI, 1 boosted PI or 1 INSTI;
- NRTI-sparing triple ARV regimen (e.g. 1 NRTI + 1 NNRTI + 1 InSTI);
- Dual therapy with protease inhibitor (such as boosted PI + NRTI or NNRTI or InSTI).

We will exclude the following regimens:

- Two-drug combinations with: 1 NRTI + 1 NNRTI, 1 NRTI + 1 PI without RTV, 1 NRTI + RAL, 2 NRTIs, MVC + RAL (not recommended by EACS guidelines);
- Triple NRTIs combination (not recommended by EACS guidelines);
- Dual therapy with DTG other than PI-based dual regimens, such as DTG + NRTI or DTG + NNRTI (simplified regimen already);
- PI monotherapy (simplified regimen already).

### 3.7 Risks / Benefits

The main risk in this trial is virological failure on DTG + FTC dual therapy. In the ART Cohort Collaboration of 18 cohorts from Europe and North America including about 17900 patients, low level viremia measured between 50 and 199 copies/ml was weakly associated with virological failure (aHR 1.38, 95%CI 0.96-2.00) (85). We will measure HIV-1 RNA level in the plasma on a regular basis to monitor for low level viremia. Any patient with HIV-1 RNA  $\geq 100$  copies/ml will undergo an additional HIV-1 RNA measurement 14 days later ( $\pm 5$  days), as well as additional adherence session and review of concomitant medications and dolutegravir and emtricitabine plasma concentration measurements.

We will define virological failure as plasma HIV-1 RNA  $\geq 100$  copies/ml on two consecutive measurements. Any patient reaching virological failure will be assessed for genotypic resistance and pharmacogenetic analyses. This latest analysis will be only done in patients who are included in the SHCS and have also signed a consent form for genetic studies. In case of virological failure, the patient will undergo an additional medical visit with review of adherence, concomitant medications, discussion of results of DTG + FTC plasma concentration. Patients randomised in the DTG + FTC dual therapy arm will be switched to a standard cART regimen while waiting for results of genotypic resistance. Patients randomised in the continuing cART arm will await results of the genotypic results. In both cases, treatment will be adjusted according to genotypic resistance results. All failing patients will complete study procedures until week 48. Figure 3 presents the algorithm for the management of virological failure.

Any patient with HIV-RNA between 20 and 99 copies at any time of scheduled visits will have an additional HIV-RNA measurement after 6 weeks (+/-5 days).

Figure 3: Algorithm for the management of virological failure

[figure not shown]

Other risks associated with the trial consist of the occurrence of DTG-related side effects as observed in phase III trials and observational studies, and described in section 3.2. Side effects were relatively uncommon, with the exception of CNS adverse events in observational studies. These CNS side effects led to few discontinuation of the drug. However, patients randomised in the DTG + FTC dual therapy arm and “new” to DTG will be evaluated for CNS symptoms using a standardised questionnaire at week 2 (by phone call by the study nurse/physician) and at week 6.

Emtricitabine is a well tolerated drug with little toxicity: in trials of patients with HIV or HBV infection, adverse events occurring with at least 10% frequency include gastro-intestinal symptoms with 14% to 18% of nausea and 9% to 24% of diarrhea, asthenia (10%-16%) and headache (12%-18%) (69). Very few of the adverse events were categorized as serious.

Potential benefits to participants may include a simplification of antiretroviral therapy and a decrease in potential side effects related to other antiretroviral drugs.

### **3.8 Justification of choice of study population**

This maintenance trial will enroll HIV-positive individuals on first-line or maintenance antiretroviral therapy who are virologically suppressed and included in the SHCS or getting care from a medical doctor of the SHCS network. The SHCS is highly representative of the HIV epidemic in Switzerland with an estimated coverage of 75% of HIV-infected individuals, 69% of all patients with AIDS in Switzerland, and 72% of all ART-treated individuals. Patients will be recruited during routine consultations in the outpatient clinics of the participating sites of the SHCS network. The study does not foresee inclusion of vulnerable participants or enrolment in emergency situations.

## **4. STUDY OBJECTIVES**

### **4.1 Overall Objective**

The purpose of this study is to evaluate whether maintenance antiretroviral therapy could be simplified to DTG + FTC dual therapy and/or patient-centered monitoring once virological suppression is achieved. Using a factorial design, the study aims to assess the efficacy of DTG + FTC dual therapy to maintain virological suppression through 48 weeks of follow-up as well as the costs of a patient-centered ART laboratory monitoring. The study will also describe the safety and acceptability of the different study arms.

### **4.2 Primary Objective**

The study seeks primarily to assess:

- The efficacy of DTG + FTC dual therapy to maintain virological suppression throughout 48 weeks in virologically suppressed HIV-infected individuals who are switched from standard therapy to DTG + FTC dual therapy.
- The costs from the perspective of the health care provider of a patient-centered ART monitoring strategy which offers alternative options for the conduction of study visits, venipunctures, drugs delivery, and which omits CD4 cell count, lipid and glucose measurements, and safety blood tests (CK, renal, liver and full blood count) during follow-up.

### **4.3 Secondary Objectives**

Secondary objectives are to assess:

- Loss of future drug options in patients with virological failure, predictors of virological failure, time to loss of virological response (TLOVR), change in CD4 cell count, change in HIV-DNA blood reservoir, adherence, DTG and FTC plasma concentration, safety, treatment satisfaction, acceptability, health-related quality of life, costs of treatment arms;
- Acceptability, safety, cost-effectiveness, and health-related quality of life of monitoring arms.

### **4.4 Safety Objectives**

The study aims to assess the safety of DTG + FTC dual therapy and simplified ART monitoring throughout 48 weeks by evaluating the following parameters:

- Loss of future drug options in case of virological failure defined as new intermediate or high-level resistance to one or more drugs to which the patient's virus was considered sensitive at trial entry;
- Change in CD4 cell count, total cholesterol, low density lipoprotein-cholesterol, Framingham-calculated cardiovascular risk, and glomerular function rate;
- Occurrence of adverse events;
- Occurrence of serious adverse events;
- Occurrence of CNS adverse events in patients new to DTG.

## 5. STUDY OUTCOMES

### 5.1 Primary Outcomes

The *first primary outcome* for the comparison between DTG + FTC dual therapy and standard cART is the proportion of patients maintaining HIV suppression defined as HIV-RNA <100 copies/ml throughout 48 weeks (+/- 21 days). A single blip defined as HIV-RNA <200 copies/ml during the study period is allowed as long as this value is followed by HIV-RNA <50 copies/ml.

The *second primary outcome* for the comparison between patient-centered and standard monitoring is the direct costs of the two study arms from the health care system perspective at week 48.

### 5.2 Secondary Outcomes

1. Proportion of patients maintaining HIV suppression defined as HIV-RNA <50 copies/ml throughout 48 weeks (+/- 21 days). A single blip defined as HIV-RNA <200 copies/ml during the study period is allowed as long as this value is followed by HIV-RNA <50 copies/ml;
2. Proportion of patients with HIV-RNA < 50 cp/ml at week 48 by FDA snapshot analysis; Proportion of patients experiencing loss of future drug options defined as new intermediate or high-level resistance to one or more drugs to which the patient's virus was considered sensitive at trial entry;
3. Time to loss of virological response (TLOVR) up to week 48 defined as the first of the two-confirmed HIV-RNA >100 copies/ml (at least two weeks apart);
4. Change in CD4 cell count from baseline to week 48 +/- 21 days;
5. Change in HIV-DNA level from baseline to week 48 +/- 21 days;
6. Change in lipidic profile (total cholesterol, high density lipoprotein-cholesterol, triglycerides, and low density lipoprotein-cholesterol) from baseline to week 48 +/- 21 days;
7. Change in glucose profile from baseline to week 48;
8. Change in Framingham-calculated cardiovascular risk from baseline to week 48;
9. Change in glomerular function rate from baseline to week 48;
10. Proportion of patients with an adverse event throughout week 48;
11. Proportion of patients with a serious adverse event (SAE) throughout week 48;
12. Proportion of patients with a CNS adverse event throughout week 48;
13. Proportion of patients new to DTG with CNS symptoms at 2 and 6 weeks after starting DTG;
14. Change in patients' health-related quality of life from baseline to weeks 12 and 48;
15. Assessment of patient's monitoring satisfaction from baseline to weeks 24 and 48 for patients in the patient-centered monitoring arm;
16. Assessment of the global satisfaction of the monitoring at week 48 for all patients (regardless of the randomisation arm);
17. Proportion of patients in the patient-centered monitoring arm expressing willingness to change monitoring options throughout 48 weeks;
18. Assessment of patient's treatment satisfaction at week 48;
19. Assessment of ARV treatment in the post study;
20. Study satisfaction at week 48;
21. Cost-effectiveness of study arms at 48 weeks;
22. Changes in patient weight from baseline to week 48.

### 5.3 Other Outcomes of Interest

1. Assessment of patient adherence to treatment throughout 48 weeks of follow-up;
2. Number of extra-visits performed outside trial scheduled throughout 48 weeks.

### 5.4 Safety Outcomes

1. Change in CD4 cell count from baseline to week 48;
2. Change in lipidic profile (total cholesterol, high density lipoprotein-cholesterol, triglycerides, low and high density lipoprotein-cholesterol) from baseline to week 48;
3. Change in glucose profile from baseline to week 48;
4. Change in Framingham-calculated cardiovascular risk from baseline to week 48;

5. Change in glomerular function rate from baseline to week 48;
6. Proportion of patients with an adverse event at week 48;
7. Proportion of patients with a serious adverse event at week 48;
8. Proportion of patients with a CNS adverse event throughout 48 weeks
9. Proportion of patients new to DTG with CNS symptom at 2 and 6 weeks after starting DTG;
10. Changes in patient weight from baseline to week 48.

## **6. STUDY DESIGN**

### **6.1 General study design and justification of design**

This is a pragmatic multicentre, 2 x 2 factorial randomized controlled trial with 1:1:1:1 randomization to switching to DTG + FTC dual therapy or continuation of cART and to patient-centered monitoring or continuation of standard monitoring (Figure 4).

[figure not shown]

Figure 4: Schematic presentation of study design DTG + FTC dual therapy

HIV-infected patients virologically suppressed for at least 24 weeks on standard cART will be randomly allocated:

- Standard-of-care arm: patients randomized in this arm will continue their current cART regimen, according to section 7.1.
- Dual therapy arm: patients randomized in this arm will be switched to DTG + FTC dual therapy. DTG 50 mg and FTC 200 mg will be administered once daily as dual therapy for a duration of 48 weeks.

For all patients, HIV-RNA measurements will be performed at screening, baseline, week 6, week 12, and every 12 weeks afterwards. Any patient with HIV-RNA between 20 and 99 copies/ml at any time of scheduled visits will have an additional HIV-RNA measurement after 6 weeks ( $\pm 5$  days). Any patient with HIV-RNA  $> 100$  copies/ml at any time of scheduled visits will have an additional HIV-RNA measurement after 2 weeks ( $\pm 5$  days).

### **Patient-centered monitoring**

Randomization will also allocate patients into the following two groups:

- Standard monitoring arm: patients randomized in this arm will continue a standard 12-weekly routine immunological and safety blood monitoring, including CD4 cell count, lipids and glucose, renal and hepatic function tests, creatine kinase at their affiliated SHCS sites.
- Patient-centered monitoring arm: patients randomized in this arm will have immunological and safety blood analyses (CD4 cell count, lipids and glucose, renal and hepatic function tests, creatine kinase) performed at screening and at week 48. Additional safety blood tests will be performed in case of signs and symptoms as indicated by the physician. In addition, patients will have to choose at least one of three alternative options for the conduction of study visits, venipuncture and drugs delivery at weeks 6, 12 and 36, see section 8.1.1. Patients will also have the opportunity to change or give their opinion on the alternative option(s) chosen if they find it non convenient during the study. Changes will be possible at week 24; satisfaction will be assessed at week 12, 24, 36 and 48.

Importantly, all interventions or blood measurements potentially related to adherence (affecting the primary endpoint) will be identical between the study arms (see section 8.4).

## **6.2 Methods of minimising bias**

### **6.2.1 Randomisation**

#### Allocation sequence

Patients will be randomised 1:1:1:1 using randomly-permuted blocks of varying sizes to one of the four study arms (one computer-based randomization list stratified per study center).

#### Concealment mechanism

Each of the 7 centres will receive the attribution number using a central computer-based randomization system.

#### Implementation

One allocation sequence stratified per study center will be generated by an independent team who will not be involved in the implementation of the study on sites using a computer-generated sequentially numbered randomization list. Lists will be transferred to the electronic case report form based on a standardized process. The process ensures that lists are stored with restricted access so that only system administrators have access. Once eligibility criteria are confirmed and when the patient has provided oral written consent to participate in one of the 7 centers enrolled in the trial, the study nurse on site (or the study investigator) will register the patient in the electronic data capture system after which the allocation will be revealed.

### **6.2.2 Blinding procedures**

This will be an open-label trial.

### **6.2.3 Other methods of minimising bias**

The use of validated questionnaires on adherence, health related quality of life and treatment satisfaction will help minimising information biases. The following validated questionnaires will be used:

- Adherence will be measured using the questionnaire reported by Glass, Sterne et al. 2015 (86) and used during routine HIV consultations within the SHCS.
- Health related quality of life will be measured using the PROQOL-HIV questionnaire (87, 88) together with a visual analog scale.
- Central nervous system symptoms will be assessed using the depression module PHQ-9 recommended by the WHO (89, 90).

### **6.3 Unblinding Procedures (Code break)**

Not applicable. This is an open-label trial.

## 7. STUDY POPULATION

HIV-1 positive individuals included in the SHCS or getting care from a medical doctor of the SHCS network will be enrolled in this maintenance trial. All SHCS centres will participate in the study. Patients relocating within Switzerland can be followed in any of the participating SHCS centres.

### 7.1 Eligibility criteria

Participants fulfilling all of the following inclusion criteria are eligible for the study:

1. Informed consent as documented by signature
2. Documented HIV-1 infection;
3. Enrolled in the SHCS or receiving care from a medical doctor of the SHCS network;
4.  $\geq 18$  years of age;
5. HIV-RNA  $< 50$  copies/mL at screening and for at least 24 weeks before screening on effective suppressive cART, one blip with less than 200 copies/mL allowed during this period if followed by at least 2 results  $< 50$  copies/mL;
6. On standard cART at the time of inclusion, i.e.:
  - 2 NRTIs + either 1 NNRTI, 1 boosted PI or 1 INSTI;
  - NRTI-sparing triple ARV regimen (e.g. 1 NRTI + 1 NNRTI + 1 INSTI);
  - Dual therapy with protease inhibitor.

Every effort will be made to include women (91) in the same proportion as in the prospective SHCS (28% of HIV-infected individuals included into the SHCS are female; SHCS website demographic data, accessed 20 December 2017).

The presence of any of the following exclusion criteria will lead to exclusion of the participant:

1. HIV-2 infection;
2. Previous ART change for unsatisfactory virological response, i.e. slow initial virological suppression, incomplete suppression or rebound; change for convenience or toxic effect prevention or management allowed.  
*Note: patients with documented genotype(s) presenting only a M184V mutation remain eligible;*
3. Creatinine clearance  $< 50$  mL/min;
4. ASAT or ALAT  $> 2.5$ x upper limit of the norm;
5. Known hypersensitivity, intolerance or allergy to DTG or FTC;
6. Known or suspected non-adherence (defined as  $< 80\%$  adherence, i.e. missed dose  $> 1$ x/week), to current treatment in the last 24 weeks;
7. Concomitant use of drugs that decrease dolutegravir blood concentrations including carbamazepine, oxcarbamazepine, phenytoin, phenobarbital, St John's wort and rifampicin;
8. Women who are pregnant or breast-feeding;
9. a. Presence of any INSTI-resistance. (92).  
b. Non availability of previous routine resistance test, at least for reverse transcriptase and protease genes.  
*Note: Subjects remain eligible in the absence of any previous resistance test only if they are on their first-line antiretroviral regimen;*
10. Evidence of acute or chronic hepatitis B virus infection based on results of serology testing as follows:
  - subjects positive for HBsAg are excluded (corresponding to acute or chronic infection);
  - only positive anti-HBc subjects will be excluded if positive HBV-DNA;
  - susceptible\* (negative HBsAg, anti-HBc and anti-HBs), immune due to hepatitis B vaccination (negative HBsAg and anti-HBc and positive anti-HBs) and immune due to natural infection (negative HBsAg and positive anti-HBc and anti-HBs) subjects are not excluded.

---

\* HBV-susceptible subjects will be offered with immunization as standard-of-care practice.

Patients enrolled in other interventional studies are not eligible. After the other interventional study termination, they will have to wait at least 3 months before the Simpl'HIV screening.

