### 9.2.2 Assessment of Secondary Outcomes

- Proportion of patients with HIV-RNA <50 cp/ml at week 48 by FDA snapshot. The following assumptions will be done:
  - a. Success is considered as HIV-RNA < 50 cp/ml in the snapshot time window;
  - b. Failures will be defined as one of the following categories, i.e.:
    - i. HIV-RNA  $\geq$  50 cp/ml;
    - ii. Change of therapy
    - iii. Discontinuation of therapy due to lack of efficacy;
  - c. No virological data will be defined as one of the following categories, i.e.:
    - i. Discontinued due to adverse event or death;
    - ii. Discontinuation of therapy due to consent withdrawal or loss to follow-up or other reason;
    - iii. Patients that are on study but have missing data in snapshot time window;
  - d. Snapshot time window is 48 weeks after the baseline visit  $\pm$  3 weeks (i.e. window size is half of the duration of the time between study visits);
- Loss of future drug options will be assessed in patients failing treatment, i.e. patients who will have 2 consecutive HIV RNA measurements  $\geq$ 100 copies/ml. For these patients, genotype resistance testing will be performed at the SHCS center according to their usual practice. Plasma samples will be collected at each visit, processed and stored at  $-80^{\circ}\text{C}$  at local virology laboratories. The same processing and storage conditions will be used as for SHCS samples. Genotype resistance interpretation will be centrally repeated by the Laboratory of Virology at HUG at the end of the study.
- CD4 cell count change: measurement of the CD4/CD8 fraction at local immunology or virology laboratories.
- HIV-DNA level change: HIV-DNA level will be measured in batch by a digital droplet PCR (ddPCR) assay using the RAINDANCE system. PBMC samples will be stored at randomization and at week 48 visit and the assay will be performed retrospectively in the Division of Infectious Diseases and Hospital Epidemiology, University hospital Zurich
- Lipidic profile changes: measurement of total cholesterol, LDL-cholesterol, HDL-cholesterol and triglycerides at local chemistry laboratories.
- Glucose level changes: measurement of glucose at local laboratories.

- Framingham-calculated cardiovascular risk changes: calculation using the Framingham 10 year CHD risk calculator by MDCalc: <http://www.mdcalc.com>. A printout of the result should be filed with the source documents.

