### 11.3 Statistical criteria of termination of trial

This is an open label study. The laboratory results that define treatment failure (HIV-RNA) of all participants included will be available within a week to the investigators. A detailed report including a summary of Serious Adverse Events, grade 3/4 Adverse Events, laboratory toxicities as well as virological failures, pregnancies and safety signals will be sent to the DSMB on a 6-monthly basis.

To protect the safety of the study participants, a safety interim analysis on the first 100 patients randomized will be done once reached the end of the time window for their 24 weeks study visit. The following data will be reviewed:

Safety data:

- Participant recruitment, accrual, retention and withdrawal information
- Adverse events (AEs) and serious adverse events (SAEs)
- Pregnancies
- Laboratory values
- Additional virological tests performed outside study schedule
- Any other safety-supporting data requested by the DSMB

Efficacy data:

- HIV-RNA data (primary endpoint measure)
- Genotype resistance test data (secondary endpoint)

We will also convene the DSMB in the following situations:

- (1) if > 2 patients experienced virological failure and a new resistances on DTG + FTC dual therapy before the planned interim safety analysis is done;
- (2) if new published or unpublished data show any major inconvenience of testing a DTG + FTC dual therapy arm.

The DSMB will then give recommendations regarding the continuation, modification or termination of the trial.

Stopping rules:

The DSMB may recommend stopping the trial for the following reasons:

- The data show a significantly increased risk of serious adverse events in one of the study groups;
- On the basis of a positive efficacy result only when the data are truly compelling and the risk of a false positive conclusion is acceptably low. The trial will only be stopped for positive efficacy if a strong statistically and clinically significant difference in virological success is seen between treatment arms;
- If interim data suggest that the simplified treatment/monitoring arm under study is of no benefit (trend indicating clear inferiority of the simplified treatment/monitoring arm), or that accrual rates are too low and/or that noncompliance is too great to provide adequate power for identifying the specified benefit, the DSMB may consider whether continuation of the study is futile and may recommend termination on this basis;

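### Resistance found at failure can be scored as new although the gene was never sequenced before entry

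*Protocol*

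**What the plan says.** **Eligibility (Section 7.1).** Exclusion 9a is "Presence of any INSTI-resistance". Exclusion 9b is "Non availability of previous routine resistance test, at least for reverse transcriptase and protease genes", so a patient can satisfy it with no integrase sequence. The note to 9b goes further: "Subjects remain eligible in the absence of any previous resistance test only if they are on their first-line antiretroviral regimen". Exclusion 2 removes patients with "Previous ART change for unsatisfactory virological response, i.e. slow initial virological suppression, incomplete suppression or rebound", but its note keeps patients whose documented genotype shows only M184V.

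**Outcome (Section 5.2, same wording in 4.4 and 11.4.5).** Loss of future drug options is "new intermediate or high-level resistance to one or more drugs to which the patient's virus was considered sensitive at trial entry". Section 11.4.5 compares the proportion between the treatment arms.

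**Genotyping.** The entry information collected is the historical genotype (Section 9.2.3). Within the trial, a genotype is run only after two consecutive HIV-RNA results of at least 100 copies/ml (Sections 3.7 and 9.2.2). The central repeat in Section 9.2.2 concerns interpretation; no sequencing of an entry sample is planned.

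**Stored material (Section 9.2.2).** "PBMC samples will be stored at randomization and at week 48 visit". These cells are intended for measuring the HIV-DNA level.

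**The concern.** Whether dual therapy costs patients future drug options is a central safety question for a de-escalation trial. The answer depends on the word new, and new can be judged only against a known starting point. The protocol admits patients for whom that starting point was never measured in one gene, or in any, and does not say how they are classed. Read literally, a virus that was never tested and is presumed free of resistance counts as sensitive on entry. A mutation it already carried then becomes a lost drug option when it surfaces at failure. Part of the result would depend on whether an old laboratory report exists and not on what happened under treatment.

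**Working it through.** **1. Can 9a be checked for everyone enrolled?** It needs an integrase sequence. 9b does not ask for one, and the first-line note waives testing altogether. For patients without that sequence, 9a can only be presumed to be met.

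**2. Do other criteria close the gap?** Exclusion 2 applies to a previous change of regimen for poor response. A first-line patient who rebounded and re-suppressed on the same drugs changed nothing, and inclusion 5 looks back only 24 weeks before screening. Integrase-based regimens are admitted by inclusion 6, and switches for convenience or toxicity are allowed. Earlier integrase-inhibitor exposure without an integrase sequence is therefore possible. The documents give no frequency for either situation.

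**3. How is the same mutation scored?** Take M184V found at confirmed failure:
- documented before entry: not new;
- earlier reverse transcriptase sequence without it: new;
- no earlier sequence, mutation archived: new if sensitivity is presumed, not assessable otherwise. The protocol does not choose.

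**4. How many patients could be affected?** The protocol states no figure for this, so none can be reproduced. Inputs: 92 per treatment arm, with 94% suppressed on DTG + FTC and 97% on cART (Section 11.2).
- DTG + FTC: 92 × 0.06 = 5.5 non-suppressed expected.
- cART: 92 × 0.03 = 2.8.
- With the 92% suppression assumed in the synopsis for both arms: 92 × 0.08 = 7.4 per arm.

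These figures overstate the number genotyped. Genotyping needs two consecutive results of at least 100 copies/ml, and Section 11.5 counts patients with no HIV-RNA at weeks 36 and 48 as failures without any genotype. Only those also lacking an entry sequence are exposed.

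**5. What does one case do?** 1/92 = 1.1 percentage points in an arm.

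**6. Illustration.** Let a be the share of failures whose archived resistance is counted as new. This is an assumption; the documents give no value. Treating all 6% as genotyped failures, the chance of at least one misclassified DTG + FTC patient is 1 − (1 − 0.06a)^92:
- a = 5%: 1 − 0.997^92 = 24.1%;
- a = 10%: 1 − 0.994^92 = 42.5%;
- a = 20%: 1 − 0.988^92 = 67.1%.

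Fewer genotyped failures would lower all three.

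**The case against.** The strongest reply is that the protocol nowhere says archived mutations count. An untested gene may be read as sensitive by default or as not assessable, and Section 11.4.6 leaves the detail of secondary analyses to a statistical analysis plan that is not at hand. This stands as far as it goes: misclassification is permitted, not prescribed. It does not remove the point. The outcome definition and the planned use of the stored cells are fixed in the protocol, and without a rule the choice would be made in an open-label trial after a case has appeared.

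Exposure is also limited. The full waiver covers first-line patients only, other patients have reverse transcriptase and protease results, and exclusion 2 removes many likely carriers. Section 11.2 already concedes low power for resistance. All of this stands and keeps the point small.

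Randomisation should balance archived resistance at entry. It does so in expectation for carriage. Resistance is observed only in patients who fail, however, and the protocol's own rates expect twice as many of those on DTG + FTC (5.5 against 2.8). An equal archived share among failures would then yield about twice as many misclassified cases in that arm.

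A reader might also infer that archived mutations would set off the ad hoc DSMB meeting in Section 11.3 ("if > 2 patients experienced virological failure and a new resistances on DTG + FTC dual therapy"). The documents give little support for this. The trigger covers dual-therapy patients before the interim analysis, does not tie new to trial entry, and only convenes the board. Take about 50 such patients (half of the first 100), 6% failure and 10% of failures with truly emergent resistance. The chance of more than two cases is then 0.3% with no archived resistance miscounted, 2.0% if 10% of failures carry it and 5.2% if 20% do. An unnecessary meeting errs on the cautious side.

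**Conclusion.** The gap is real and narrow. For any gene without an entry sequence, sensitivity on entry is presumed, and a mutation that predates randomisation can be scored as loss of future drug options. The effect is confined to a secondary and safety outcome; the non-inferiority comparison on HIV-RNA is untouched. The population at risk is some fraction of about 5.5 non-suppressed patients expected on DTG + FTC, and of about 2.8 on cART, at the Section 11.2 rates. That fraction cannot be stated, because the documents give neither the share of untested patients nor the prevalence of archived resistance. The point matters because resistance cases will be so few that one wrong classification changes the reading of the result.

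Three stronger conclusions are not supported. It cannot be said that archived mutations will be counted, only that they can be. Pooled non-suppression over both arms (2.8 + 5.5 = 8.3 patients, or 184 × 0.08 = 14.7 at the synopsis rate) is not a count of genotyped failures, still less of misclassified ones. Nor is there a case for changing eligibility: admitting first-line patients without a genotype is an explicit choice, and the defect lies in the outcome definition.

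**What to change.** In Sections 5.2, 9.2.2 and 11.4.5, with 4.4 kept in line:
- count resistance as new only if a pre-randomisation sequence of that gene lacks the mutation;
- for a confirmed failure without such a sequence, sequence that gene from the cells already stored at randomisation;
- if that does not succeed, report the case as entry status unknown, separately from new resistance, and give the outcome with and without these cases.

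Leave eligibility and the DSMB trigger count unchanged, but have the report to the DSMB state for each case whether an entry sequence of the gene existed.

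The cost is wording plus sequencing of a few stored samples, with no new visit or blood draw. Some cases may remain unknown.
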